### Study cohorts

This study brings together diverse cohorts (
Table 1) under a common theme providing participants with prospectively assessed and clearly defined malnutrition exposure across populations and life-course and not previously malnourished controls, all from LMICs at various stages of the nutrition transition but with ongoing burden of infectious disease. Flow charts for each cohort are given in
Figures 2–
7.

**Table 1. T1:** Study cohorts for Severe Acute Malnutrition in children and adults - the role of the Pancreas (SAMPA).

	Cohort	Sample size-previous and expected
**1.**	** *DIVIDS (Delhi Infant Vitamin D Supplementation) study, India* ** The DIVIDS cohort comprises infants born low birth weight (LBW, <2.5 kg) at term in 2007-2010. They had monthly follow-up until 6 months ^ 14 ^ then at 5 years ^ 15 ^ and are currently, aged ~13 years. *For SAMPA, the DIVIDS cohort acts as a positive control since we expect adverse long-term non-communicable disease consequences of being born LBW.*	• Birth: 2079 total, all LBW • Age 5 y: 912 total, 764 (84%) BMIZ>-2, 138 (15%) BMIZ -2 to -3, 9 (1%) BMIZ<-3; 1 no anthropometry • Age ~13 y (ongoing): 647 total, 482 (75%) BMIZ>-2, 117 (18%) BMIZ -2 to -3, 48 (7%) BMIZ<-3 • Expected for SAMPA: 750 total
**2.**	** *SAM (Severe Acute Malnutrition), Lusaka, Zambia* ** This group comprises: a) 100 children who were hospitalised with malnutrition at University Teaching Hospital (UTH) between 2010 and 2014 when they were < 2 years b) 85 never-malnourished neighbourhood controls. Children were aged ~9 years at previous follow-up ^ 16 ^ and will be ~12 years for SAMPA.	• Age < 2 y: 100 malnutrition • Age 9 y: 185 total, 100 previous malnutrition, 85 no malnutrition; currently 17 (9%) BMIZ <-2 • Expected for SAMPA: 180 total

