### Assessments

The following assessments will be carried out on all consenting participants across the cohorts. Target sample sizes are as in
Table 1.
1.
**
*OGTT:*
** The primary outcome for comparing those with and without prior malnutrition across all cohorts will be glucose ≥ 7.8 mmol/L at 2 hours in a standard OGTT with 75 g glucose (in children, 1.75 g/kg body weight up to 75 g) that is, diabetes plus impaired glucose tolerance by WHO criteria.
^
23
^ Glucose in one hour samples in all participants will also be measured since this may be a better predictor of progression to diabetes due to insulin deficiency than the two-hour time point.
^
24
^ Those with OGTT compatible with diabetes will be called back for a repeat OGTT in order to determine need for referral for clinical care. Urine dipstick will also be done for ketones to assess potential need for (short-/long-term) insulin replacement therapy. Indices of beta-cell function, insulin kinetics, and insulin resistance will be modelled from glucose, insulin and C-peptide during OGTT.
^
25
^
^,^
^
26
^ Proinsulin will be measured in baseline samples only. Autoantibodies will be measured in participants with OGTT indicative of diabetes to confirm/exclude autoimmune type-1 diabetes.2.
**
*HbA1c*
**: This will be by point-of-care test (Hemocue, Angelholm, Sweden) using fingerprick blood samples for most cohorts to indicate long-term glycaemic control; for the DIVIDS cohort, HbA1c will be measured in venous blood by a commercial lab ([name] Labs, Delhi).3.
**
*Abdominal ultrasound*:** Ultrasound scans will be performed by trained sonographers or radiologists in identified health facilities. The participant will be asked to lie on the ultrasound examination bed. They will be asked to breathe in and hold their breath in order to optimise visualization of the pancreas. A curvilinear ultrasound probe (2-5 MHz) will be placed onto the participant’s abdominal wall in the upper abdomen to image the pancreas. Images of the pancreas will be recorded and saved. Parameters obtained from the scans will be pancreas size, duct size, calcification, or other abnormality.4.
**
*Exocrine pancreas markers:*
** These will be serum lipase in baseline OGTT samples and faecal elastase: Participants will collect faecal samples either in the clinic or bring them from home.5.
**
*Urine glucose and ketones by dipstick*
**: These will be from random urine collection.6.
**

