### Statistical analyses and sample size calculations

Analyses related to individual hypotheses are described below. Primary analyses will be conducted for each cohort separately. Pooled analyses using all or some cohorts combined will be conducted based on the individual cohort results, and in order to investigate how age at malnutrition and length of time between malnutrition and outcome assessment influence the associations between malnutrition and pancreas structure and function. Analyses will be guided by the conceptual framework in
Figure 1. Sample sizes for the specific hypotheses indicate that, with the available number of participants in the cohorts, we have sufficient power for the main analyses with all participants. For some expensive or labour- and participant-intensive outcomes, we had to consider cost and feasibility and have calculated power for analyses in subsets.

*Hypothesis 1:*
Prior malnutrition is associated with later abnormal pancreatic structure and endocrine and exocrine function.

Participants with and without prior wasting malnutrition, the SAMPA study primary exposure, will be compared within each cohort for all pancreas structure and function outcomes: diabetes by OGTT or HbA1c, exocrine function as indicated by faecal elastase and serum lipase, and pancreas size and presence of abnormalities detected by ultrasound or CT scan. We will initially fit regression models for each outcome with prior malnutrition as the main exposure, controlling for sex and for age as a continuous variable. We will investigate whether there are interactions between prior malnutrition and sex, which is known to be associated with both prior malnutrition and diabetes. We will then investigate whether the associations between malnutrition and the outcomes differ by the following variables:
•Time since malnutrition•Sitting/standing height ratio as an indicator of early life stunting•HIV status for African cohorts only (SAM Lusaka, NUSTART Lusaka, CICADA)

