Several variables – BMI, FMI, FFMI and diet pattern (using components from PCA as defined above) – have potentially complex relationships with the exposure and outcomes. These variables will be measured at the time of outcome assessment, but are assumed to reflect participants’ nutritional status and diet prior to the outcome. We will start by investigating the associations among diet patterns, BMI, FMI and FFMI at the time of pancreas testing. We will then explore several relationships between these variables, the prior malnutrition exposure, and the outcomes. First, BMI and FMI may be on the causal pathway from wasting malnutrition to diabetes since recovery from wasting malnutrition associated with infection may lead to excess fat deposition,
^
30
^
^,^
^
31
^ and since people previously severely malnourished may, if it becomes possible later, choose to gain weight as a buffer against future food shortages. Second, BMI, FMI and diet patterns could be modifiers of the association between prior malnutrition and diabetes, as seen previously for diet pattern and BMI in Chinese famine survivors.
^
32
^ Third, exocrine pancreas abnormalities which result in fat malabsorption or intestinal discomfort may induce participants to modify their diets which could result in changes to BMI, FMI or FFMI.

We will conduct exploratory analyses to investigate the mechanisms through which the exposure variable, malnutrition, is associated with pancreas outcome variables. For example, decreased production of incretins by gut epithelial cells may be associated with both exocrine pancreas function, which could affect rate of absorption of nutrients which trigger incretin secretion, and insulin secretion.

**
*Sample size*
**: Large variations in prevalence of impaired glucose tolerance (OGTT≥7.8 mmol/L
*)* or high fasting glucose in never malnourished (2%-11%) make estimates imprecise. The absolute difference in prevalence of hyperglycaemia in those with prior malnutrition versus those without was 3% to 9% in these studies.
^
32
^
^–^
^
34
^ Assuming an intermediate prevalence of OGTT ≥7.8 mmol/L of 7% in those without malnutrition, the CICADA and St-ATT cohorts individually have 80% power to detect a difference in prevalence of 7.5% in those with malnutrition. For continuous variables,

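### The sufficient-power statement is not supported for the binary primary outcome in SAM Lusaka, NUSTART Lusaka and CLHNS, and in DIVIDS it depends on the age at which exposure is classified

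*Protocol article*

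**What the plan says.** Under Assessments, the OGTT item fixes one binary outcome for every cohort: "The primary outcome for comparing those with and without prior malnutrition across all cohorts will be glucose ≥ 7.8 mmol/L at 2 hours".

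Under Statistical analyses and sample size calculations, the unit of analysis is the cohort: "Primary analyses will be conducted for each cohort separately". The same paragraph states that "with the available number of participants in the cohorts, we have sufficient power for the main analyses with all participants", and sets this against the costly or burdensome outcomes, for which power was worked out in subsets.

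The Hypothesis 1 sample size text gives the only power figure for the binary outcome. It starts from a baseline, "Assuming an intermediate prevalence of OGTT ≥7.8 mmol/L of 7% in those without malnutrition", and concludes that "the CICADA and St-ATT cohorts individually have 80% power to detect a difference in prevalence of 7.5% in those with malnutrition". It also gives the range seen in earlier studies: "The absolute difference in prevalence of hyperglycaemia in those with prior malnutrition versus those without was 3% to 9% in these studies". No binary-outcome power is given for DIVIDS, SAM Lusaka, NUSTART Lusaka or CLHNS. For continuous variables, the text says that the smallest cohort can detect 0.4 SD with 90% power.

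**The concern.** The general sentence covers the main full-sample analyses, and those are cohort-specific. A reader will therefore take the primary comparison in each cohort to be adequately powered. The article shows this for two cohorts of six, and its own inputs do not bear it out for at least three of the others.

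What is at stake is how null results are read. Hypothesis 1 concerns wasting at any age. SAM Lusaka and CLHNS carry the evidence on severe malnutrition in the first two years of life, and NUSTART Lusaka carries HIV-related wasting in Zambia. A non-significant result there, set beside a statement of sufficient power, would suggest no long-term effect when the cohort could not reliably have shown one. The article also makes pooling depend on the individual cohort results, so imprecise cohort findings could influence which cohorts are combined.

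**Working it through.** **Inputs.** Prevalence of 7% in the unexposed and 14.5% in the exposed (7% + 7.5 points), from the Hypothesis 1 sample size text. Group sizes come from Table 1, with the recorded exposure proportion applied to the number expected for SAMPA:

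- SAM Lusaka: 100:85 applied to 180 gives 97 exposed, 83 unexposed.
- NUSTART Lusaka: 200 exposed, 50 + 50 = 100 unexposed.
- CLHNS: 143 exposed, 420 − 143 = 277 unexposed.
- DIVIDS ("Expected for SAMPA: 750 total"), age 5 ("Age 5 y: 912 total, 764 (84%) BMIZ>-2, 138 (15%) BMIZ -2 to -3, 9 (1%) BMIZ<-3"): (138 + 9)/911 = 16.1%, giving 121 v 629.
- DIVIDS, age about 13: (117 + 48)/647 = 25.5%, giving 191 v 559.
- St-ATT, BMI below 18.5: (189 + 216)/900 = 45%, giving 270 v 330.
- CICADA, BMI below 18.5: (73 + 74 + 105 + 103 + 109 + 171)/1947 = 635/1947 = 32.6%, giving 461 v 951.

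The text gives no significance level; two-sided 5% is assumed.

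**Formula.** With d = 0.075, n_u and n_e the unexposed and exposed numbers, and p̄ their weighted mean prevalence:

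- SE0 = √[p̄(1 − p̄)(1/n_u + 1/n_e)]
- SE1 = √[0.07 × 0.93/n_u + 0.145 × 0.855/n_e]
- power = Φ[(d − 1.96 × SE0)/SE1]

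**The plan's own figure first.** St-ATT: SE0 = 0.0250, SE1 = 0.0256, z = 1.01, power 84%, or 81% with a continuity correction. CICADA: SE0 = 0.0166, SE1 = 0.0184, z = 2.31, power 99%. The stated 80% is reproduced closely for St-ATT and holds as a floor for CICADA.

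**Other cohorts, same method:**

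| Cohort (exposed v unexposed) | SE0 | SE1 | z | Power | Continuity-corrected | Detectable at 80% power |
|---|---|---|---|---|---|---|
| SAM Lusaka (97 v 83) | 0.0469 | 0.0454 | −0.37 | 36% | 27% | 14.7 points |
| NUSTART Lusaka (200 v 100) | 0.0398 | 0.0356 | −0.08 | 47% | 38% | 11.7 points |
| CLHNS (143 v 277) | 0.0303 | 0.0332 | 0.47 | 68% | 62% | 8.9 points |
| DIVIDS, age 5 (121 v 629) | 0.0273 | 0.0336 | 0.64 | 74% | 69% | 8.3 points |
| DIVIDS, about age 13 (191 v 559) | 0.0239 | 0.0277 | 1.02 | 85% | 81% | 7.0 points |

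SAM, NUSTART Lusaka and CLHNS stay below 80% even with a one-sided test (48%, 60%, 78%).

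**Varying the baseline and the effect.** The article puts the prevalence in the never malnourished at 2% to 11%.

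| Cohort | 7.5 points from 2% | 7.5 points from 11% | 9 points from 7% | 3 points from 7% |
|---|---|---|---|---|
| SAM Lusaka | 56% | 28% | 46% | 10% |
| NUSTART Lusaka | 71% | 38% | 60% | 12% |
| CLHNS | 90% | 56% | 80% | 20% |
| DIVIDS, age 5 | 93% | 62% | 85% | 23% |

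At 3 points no single cohort exceeds about 50% (CICADA).

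**Continuous outcomes.** Power for 0.4 SD is Φ[0.4/√(1/n_u + 1/n_e) − 1.96]. SAM Lusaka, the smallest cohort: Φ(2.675 − 1.96) = 76%. NUSTART Lusaka: Φ(3.266 − 1.96) = 90%. The stated 90% fits NUSTART Lusaka, not the smallest cohort.

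**All six cohorts, stratified.** Inverse-variance weighting of the six risk differences, at 7% v 10% in each and with age-5 DIVIDS, gives SE = 1.03 points. Power is Φ(3/1.03 − 1.96) = 83%.

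**The case against.** The strongest reply is that the article never says in so many words that every cohort is adequately powered. The sentence speaks of the cohorts together and contrasts full-sample with subset analyses. The later text names CICADA and St-ATT for the binary outcome and reaches the smallest cohort only through continuous variables. That stands against reading an explicit cohort-by-cohort claim into the sentence. It does not rescue the sentence, because the full-sample main analyses are themselves run by cohort.

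Three further points stand. First, a reader might count four failing cohorts of six, but DIVIDS falls short only if exposure is taken at age 5, and the article does not fix that age. Age 5 is the more natural prior exposure, since the age-13 round was still under way, but this is an assumption. Second, a reader might infer that CLHNS would probably miss a real effect; at 68% power it would more likely than not detect it. Only SAM (64% chance of missing) and NUSTART Lusaka (53%) are more likely to miss than to find. Third, the baseline is uncertain, and CLHNS and age-5 DIVIDS reach 80% or more from 2%, or for a 9-point difference from 7%.

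The cohorts already exist, and a condensed article may leave a full power table elsewhere. That would excuse silence, but not a positive statement that the article's own figures contradict.

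**Conclusion.** Wrong as written, and cheap to correct. For the binary primary outcome, the sufficient-power statement is supported in CICADA and St-ATT. It is not supported in SAM Lusaka (36%), NUSTART Lusaka (47%) or CLHNS (68%) at the plan's 7% v 14.5%, and in DIVIDS it turns on the exposure age (74% or 85%). The finding is firmest for SAM and NUSTART Lusaka, which fall short at all three baselines and at both ends of the cited 3 to 9 point range.

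This assumes two-sided 5%, exposure as BMI below 18.5 or BMIZ below −2 (WHZ below −3 in CLHNS, hospital-diagnosed malnutrition in SAM), and Table 1 proportions that carry over to the SAMPA sample. If exposure in St-ATT were BMI below 17, its own power would be 76% against all others (144 v 456), or 71% against BMI above 18.5 (144 v 330).

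A reader might also infer that one pooled test should become the main analysis. The documents do not require that: the cohorts differ in age, infection and time since malnutrition, and the plan sets out to study how the last of these and age at malnutrition change the association. The 83% assumes a common effect. Nor does leading with continuous glucose settle the matter, since SAM Lusaka has about 76% for 0.4 SD.

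**What to change.** - For the binary outcome, limit the sufficient-power sentence to CICADA and St-ATT, and to DIVIDS only if its exposure age supports it.
- Give power or the 80%-power detectable difference for each cohort, with the significance level, the exposure definition and the DIVIDS exposure age stated, and show how the figures move over the 2% to 11% baseline range.
- Report cohort results as estimates with confidence intervals, and say that a non-significant result in a small cohort is not evidence of no effect.
- Correct the continuous-outcome statement: about 76% for 0.4 SD in SAM Lusaka (N = 180), and 90% in NUSTART Lusaka (200 v 100).
- Report the pooled analysis for all six cohorts, stratified by cohort, whatever the individual results, as a complement to the cohort-specific primary analyses.

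The cost is wording, a short table and one stratified model. No new participants or measurements are needed. The price is a less favourable statement of power.

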**5.**	** *St-ATT (Starting Anti-TB Treatment) Cohort, Philippines* ** Between Aug 2018 and Feb 2020, the St-ATT cohort recruited 900 adults undergoing tuberculosis treatment in three provinces: Cebu, Negros Occidental and Metro Manila, encompassing urban, peri-urban and rural populations. 17% had HbA1c >=7.0% (probable diabetes in TB) with an additional 30% with HbA1c 5.8%-7.0% (‘prediabetes’/mild TB-induced hyperglycaemia). ^ 21 ^ https://www.isrctn.com/ISRCTN16347615 *This cohort will be involved in the in-depth analyses.*	• 1-2 y prior: 900 total, 495 BMI >18.5 kg/m ^2^, 189 (21%) BMI 17.0-18.5 kg/m ^2^, 216 (24%) BMI <17 kg/m ^2^ • Expected for SAMPA: 600 total
**6.**	** *CLHNS (Cebu Longitudinal Health and Nutrition Survey), Philippines* ** The mothers of the cohort were randomly selected in 1983-84 when they were pregnant. ^ 22 ^ All singleton births were included regardless of nutrition status. Since the original bimonthly follow-up surveys up to age two years, there have been 8 follow-up surveys including in 2018-2019 when 1326, ~43% of the initial birth cohort (3,080), were available. *This cohort represents our longest follow-up of malnutrition diagnosed by anthropometry.* (Earlier cohort data are available open access: https://www.cpc.unc.edu/projects/cebu).	• Birth: 28 LBW of the 143 with childhood malnutrition • Age ≤ 2 y: of 420 total to be included, 143 (34%) WHZ<-3 • Expected for SAMPA: 420 total

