### Outcome measures

*Primary outcome measures*
1.Pancreatic endocrine function: diabetes or impaired glucose tolerance (pre-diabetes) by OGTT or HbA1c, defined using World Health Organization (WHO) cut-offs
^
23
^
2.Pancreatic exocrine function: faecal elastase and serum lipase

*Secondary outcome measures*
1.Pancreas size and structure: Pancreas size and architecture using ultrasound and CT (subsets from all adult cohorts)2.Pancreatic calcification: Calcification determined by CT scan (subsets from all adult cohorts)3.Insulin production and insulin resistance:a.Mathematical modelling of blood glucose, insulin and C-peptide at three (for children) or seven (for adults) times during a 120-minute OGTT for estimation of indices of first phase, second phase and total insulin release, insulin kinetics and insulin resistance;b.Mathematical modelling of data from analytes from IVGTT measured in blood samples collected at -10, -1, 2, 4, 6, 8, 10 minutes: glucose, insulin, and C-peptide (subset from CICADA
*).*
4.Other hormonal contribution to glucose metabolism and diabetes: Incretins (gastric inhibitory polypeptide (GIP) and glucagon-like peptide-1 (GLP-1)) and glucagon at 0, 30, 60, 90 and 120 minutes during an OGTT (subsets from CICADA and St-ATT). The goal is to assess whether insulin resistance is associated with changes in endocrine signals from the gut. The area under the curve of glucagon (AUC glucagon) will be used to assess a possible presence of hyperglucagonemia, often seen in T2D subjects.5.Proinsulin: Proinsulin in baseline samples before OGTT. The baseline proinsulin levels will be used as indicator of β-cell stress/exhaustion in the fasting state where higher levels of proinsulin will indicate higher levels of β-cell stress.6.Abnormal prior pro-insulin/insulin ratio and diabetes (subset): From the CICADA cohort, measurement of pro-insulin and insulin in fasting samples collected four years previously and comparison with current diabetes by OGTT. Like the fasting proinsulin, the pro-insulin/insulin ratio in fasting samples will be used as a surrogate measure of β-cell stress.

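### The claim of sufficient power is broader than the sample size section supports: for the primary OGTT outcome, power is given for two of six cohorts and is below 80% in at least three of the others

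*Protocol article*

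**What the plan says.** All of this is in the protocol article.

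- *Statistical analyses and sample size calculations*, opening paragraph: "Primary analyses will be conducted for each cohort separately". Pooled analyses of all or some cohorts are to follow, depending on the individual cohort results. The same paragraph concludes that "we have sufficient power for the main analyses with all participants", in contrast to the costly outcomes measured in subsets.
- *Assessments*, OGTT: "The primary outcome for comparing those with and without prior malnutrition across all cohorts will be glucose ≥ 7.8 mmol/L at 2 hours".
- *Outcome measures*, primary, describes the endocrine outcome more loosely, as "diabetes or impaired glucose tolerance (pre-diabetes) by OGTT or HbA1c".
- Hypothesis 1, *Sample size*, cites a prevalence of 2% to 11% in never-malnourished people and adds that "The absolute difference in prevalence of hyperglycaemia in those with prior malnutrition versus those without was 3% to 9" per cent. Taking a base of 7% for the unexposed on the 2-hour glucose outcome, it then states: "the CICADA and St-ATT cohorts individually have 80% power to detect a difference in prevalence of 7.5% in those with malnutrition". No power for the OGTT outcome is given for DIVIDS, SAM, NUSTART Lusaka or CLHNS.
- *Study cohorts*, Table 1, says of St-ATT: "17% had HbA1c >=7.0% (probable diabetes in TB) with an additional 30% with HbA1c 5.8%-7.0" per cent. The table labels the second group as prediabetes or mild hyperglycaemia induced by tuberculosis.

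**The concern.** Per-cohort primary analyses of an outcome set for all cohorts make six primary OGTT comparisons. The general statement of sufficient power covers all six, but the calculation behind it covers two, and these include the largest cohort (CICADA, 1412). The four cohorts without a figure range from 180 to 750 participants.

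At stake is how a null result in one cohort is read. If a small cohort shows no difference, the article lets it be presented as coming from an adequately powered primary analysis. In SAM or NUSTART Lusaka, a true effect of the size the plan itself uses would be missed more often than found.

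A smaller, related matter is that the power calculation rests on 2-hour glucose alone, while the list of outcomes also admits HbA1c. The stated power belongs to only one of the two descriptions.

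**Working it through.** **Method.** Two-proportion z test, two-sided 0.05 (the article states neither the level nor the sidedness), no covariate adjustment. With n₀ unexposed, n₁ exposed, prevalences p₀ and p₁, and p̄ the weighted mean:

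power = Φ{ (|p₁ − p₀| − 1.96·s₀) / s₁ }, with s₀ = √[p̄(1 − p̄)(1/n₀ + 1/n₁)] and s₁ = √[p₀(1 − p₀)/n₀ + p₁(1 − p₁)/n₁].

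**Inputs from Table 1**, with earlier exposure proportions carried to the expected SAMPA numbers (exposed / unexposed):

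- CICADA, 1412: BMI below 18.5 in 147 + 208 + 280 = 635 of 450 + 208 + 1293 = 1951, giving 460 / 952
- St-ATT, 600: 21% + 24% = 45% below 18.5, giving 270 / 330
- CLHNS, 420: 143 / 277, as printed
- NUSTART Lusaka, 300: 200 / (50 + 50), as printed
- SAM, 180: the earlier 100 : 85 split, giving 97 / 83
- DIVIDS, 750: BMIZ below −2 at age 5 in 147 of 911, giving 121 / 629; or at about age 13 in 165 of 647, giving 191 / 559

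**The plan's own figure first.** For St-ATT at 7% v 14.5%: p̄ = 0.10375, s₀ = 0.0250, s₁ = 0.0256. Then (0.075 − 1.96 × 0.0250)/0.0256 = 1.01, so power is 84% (81% with continuity correction). CICADA gives 99%. The stated 80% is therefore met in both.

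**The smallest cohort.** For SAM: p̄ = 0.1104, s₀ = 0.0469, s₁ = 0.0454. Then (0.075 − 1.96 × 0.0469)/0.0454 = −0.37, so power is 36%.

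**All cohorts**, 7.5-point difference from three bases within the cited range, and the difference detectable with 80% power from 7%:

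| Cohort | Base 2% | Base 7% | Base 11% | Detectable from 7% (points) |
|---|---|---|---|---|
| CICADA | >99% | 99% | 96% | 4.5 |
| St-ATT | 98% | 84% | 74% | 7.0 |
| DIVIDS, exposure at about 13 | 97% | 85% | 74% | 6.9 |
| DIVIDS, exposure at 5 | 93% | 74% | 62% | 8.3 |
| CLHNS | 90% | 68% | 56% | 8.9 |
| NUSTART Lusaka | 71% | 47% | 38% | 11.7 |
| SAM | 56% | 36% | 28% | 14.7 |

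With unpooled variance, the 7% column reads: CICADA 98%, St-ATT 83%, DIVIDS 77% (about 13) or 61% (age 5), CLHNS 62%, NUSTART Lusaka 56%, SAM 38%. SAM, NUSTART Lusaka and CLHNS remain below 80%. Even for 9 points from 7%, the top of the cited range of differences, SAM has 46% and NUSTART Lusaka 60%.

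**Sensitivity of the St-ATT figure.** Power for 7.5 points is 74% at an 11% base and 62% at 17%. The detectable difference rises from 7.0 to 9.4 points at 17%.

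**The case against.** The best defence is that the binary power claim is expressly confined to CICADA and St-ATT, so a careful reader can see that the other four are not covered. The general sentence may only mean to contrast full-cohort with subset analyses, and continuous outcomes have their own power statement. The first part is fair and explains how the wording arose, but the sentence still claims sufficiency for the main analyses in a paragraph that makes each cohort's analysis primary. The continuous outcomes do not rescue it. They are different outcomes, and their claim (0.4 SD with 90% power in the smallest cohort) gives for SAM 0.4/√(1/83 + 1/97) − 1.96 = 0.715, or 76%.

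Several stronger readings are tempting but not supported.

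- **A reader might infer that four of the six cohorts fail.** The article does not fix the age at which wasting counts as exposure in DIVIDS. Power there is 74% at age 5 and 85% at about 13. At a 2% base, CLHNS and DIVIDS both exceed 80%.
- **A reader might infer from Table 1 that the St-ATT base is 17% to 47%.** Those figures are HbA1c rather than 2-hour glucose, come from people undergoing tuberculosis treatment, cover the whole cohort rather than the unexposed, and are partly labelled as induced by tuberculosis. They suggest that 7% may be low, since 17% alone exceeds the cited 2% to 11%. They do not give the right rate.
- **A reader might call the stated 80% wrong, or 7.5 points too optimistic.** The 80% reproduces for St-ATT and understates CICADA, which is conservative. The 7.5 points lie inside a range that the article discloses along with its imprecision.
- **A reader might assume that pooling makes up for the small cohorts.** The article does not commit to a pooled estimate that includes every cohort. Pooling may use only some, and follows the individual results.

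**Conclusion.** The concern holds in limited form. For the primary OGTT outcome analysed by cohort, the general statement of sufficient power is supported for CICADA and, at a 7% base, for St-ATT. It is not supported for SAM (36%), NUSTART Lusaka (47%) or CLHNS (68%), and for DIVIDS it depends on an exposure age left open. For SAM and NUSTART Lusaka the conclusion does not depend on the 7% assumption, because both fall short from 2% to 11%. St-ATT has little margin and drops below 80% at an 11% base.

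This rests on a two-sided 0.05 level, on Table 1 proportions carried to the expected numbers, and on BMI below 18.5 as the exposure in CICADA and St-ATT. With BMI below 17 (144 / 456), St-ATT would have 76%. The NUSTART Lusaka and CLHNS splits are printed, so those two results need no derived split.

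The two descriptions of the primary endocrine outcome are a lesser inconsistency. The Assessments section already fixes one outcome across cohorts and the power calculation uses it, so only the looser wording needs aligning.

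**What to change.** 1. Limit the power sentence in the opening paragraph of *Statistical analyses and sample size calculations* to the cohorts and outcomes that have the power.
2. Under Hypothesis 1, *Sample size*, give the difference detectable with 80% power from a 7% base for each cohort, with the level and exposure split used: CICADA about 4.5 points, St-ATT 7.0 (with 9.4 at a 17% base as a sensitivity figure), DIVIDS 6.9 to 8.3 depending on the exposure age, CLHNS 8.9, NUSTART Lusaka 11.7, SAM 14.7.
3. State that SAM, NUSTART Lusaka and CLHNS, and DIVIDS if exposure is taken at age 5, are not individually powered for a 7.5-point difference in the OGTT outcome, so that a null result there is inconclusive.
4. Align the primary endocrine outcome under *Outcome measures* with the single 2-hour glucose outcome under *Assessments*, which the power calculation uses.

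The cost is a few restated figures and one outcome line. No participants or measurements are added, but the stated power becomes less favourable.
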